#### Secondary outcomes

STI incidence and changes in risky sexual behaviours (i.e. condom use/number of partners/ number of unsafe partners/amount anal sex/recreational drug use/renounce to visit the STI clinic). In addition, we will monitor how care was experienced. If help seeking behaviour took place, information will be collected to know where help was obtained, and how useful the help was on a scale from 1 to 5.

### Study design

This is an open-label randomized controlled trial with a behavioural intervention to stimulate help seeking behaviour for mental health and addiction problems among MSM who show high risk behaviour for STI and HIV at the STI clinic of Amsterdam (Fig. 1). Participants will be assigned by block randomization in groups of 4, 6 or 8, with the help of a computer program.

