## Background

Men who have Sex with Men (MSM) constitute a risk group for Sexually Transmitted Infections (STI), including HIV. The STI positivity rate – chlamydia, gonorrhea, syphilis and hiv - among MSM attending the STI clinic in Amsterdam is around 18% among HIV-negative MSM and 30% among HIV-positive MSM [1]. Besides this high positivity rate, there is a high recurrence of infections in this group. More than 10% of the men who were diagnosed with an STI had a new infection within one year [1].

For MSM with a high STI risk we started a case holding cohort: the MS2 cohort. We included 107 HIV-negative and 95 HIV-positive MSM from January 2014 till April 2016 [2]. If screened 4 times a year, in 25% of each visit a new STI was found and more then 40% reported using methamphetamine, mephedrone and/or γ-Hydroxybutyric acid (GHB)/ γ-Butyrolactone (GBL) during sex [2]. Despite motivational interviewing and counseling, risk behaviour remains high.

A syndemic is two or more afflictions, interacting synergistically and contributing to an excess burden of disease. The syndemic theory holds that psychosocial problems frequently co-occur, interact and mutually reinforce each other, thereby increasing high risk behaviours and co-occurring diseases [3]. According to the syndemic theory that explains the increased risk on STI in MSM, he following domains can contribute to risk behaviour: drug use, mental health problems, stigma, past or present abuse, and discrimination [4]. Sex related drug use is high among MSM in our MS2 cohort [2], and sex-related drug use is associated with STI [5, 6], HIV [6] and high risk behaviour [7] In addition, MSM report elevated levels of mental health problems, including Attention Deficit Hyperactivity Disorder (ADHD), depressive episodes, obsessive-compulsive disorder and alcohol and drug dependence [8, 9]. If however, co-occurring psychosocial problems were assessed and treated, it might decrease high risk behaviours and co-occurring diseases.

To test this theory we developed the syndemic based intervention (syn.bas.in). The purpose of this open label, randomized controlled intervention at the STI outpatient clinic of Amsterdam is to answer the following question: does syndemic screening and indicated referral to co-located mental health and/or addiction treatment services result in increased help seeking behaviour, and decrease risk behaviour in MSM who are at high risk for STIs and HIV?

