#### Inclusion criteria

The inclusion criteria are MSM, 18 years or older, sufficient command of Dutch or English andfor HIV positive MSM at least one STI* in the last 12 months.for HIV negative MSM at least two STI* or a PEP treatment in the last 24 months.

(* i.e. urethral, pharyngeal or anal gonorrhoea; urethral, pharyngeal or anal chlamydia; lymfogranuloma venereum; syphilis; acute hepatitis B and/or C; and newly diagnosed HIV infection. Genital warts or genital herpes do not count as inclusion criteria).

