### Statistical analysis

Descriptive statistics will be used to describe baseline characteristics, questionnaire scores, condom use, number of partners, number of unprotected anal sex partners, recreational drug use (during and outside sexual activities) and lost to follow up rate. The distribution of the characteristics of the two intervention groups will be compared using Chi-squared tests for categorical data and student t-test or rank sum tests for continuous data depending on the distribution of the characteristics. To assess to effect of the intervention (control group vs. experimental group) on the primary outcome variable (help seeking behaviour), a univariable logistic regression analysis will be performed. Similar analyses will be performed with the secondary outcome variables. Changes over time will be described for the following parameters: drug use, risk behaviour and incident STIs. We will use appropriate univariable and multivariable statistical methods (poisson regression), corrected for repeated measurements within individuals to investigate changes over time and associated determinants. These analyses will be conducted comparing the two intervention groups.

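### The plan does not commit to HIV status as a covariate in the STI comparison or say which of its two STI analyses governs; adjusting for it is a small, nearly free improvement

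*Protocol article*

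**What the plan says.** All references are to the protocol article.

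- **Allocation (Study design):** "Participants will be assigned by block randomization in groups of 4, 6 or 8, with the help of a computer program". No stratification factor is named.
- **Primary comparison (Statistical analysis):** "a univariable logistic regression analysis will be performed" for help seeking.
- **Secondary outcomes, including STI incidence (same section):** "Similar analyses will be performed with the secondary outcome variables".
- **Changes over time, with incident STIs among the listed parameters (same section):** "We will use appropriate univariable and multivariable statistical methods (poisson regression), corrected for repeated measurements within individuals". The section closes with "These analyses will be conducted comparing the two intervention groups". The covariates are not named.
- **Baseline (same section):** "The distribution of the characteristics of the two intervention groups will be compared using Chi-squared tests for categorical data", with t or rank sum tests for continuous variables.
- **HIV status and STI (Background):** STI positivity at the clinic "is around 18% among HIV-negative MSM and 30% among HIV-positive MSM".
- **HIV status and eligibility (Inclusion criteria):** the rule differs by HIV status. It asks for "HIV negative MSM at least two STI* or a PEP treatment in the last 24 months", but for only one STI in 12 months from HIV-positive men. The Abstract gives 24 months for HIV-positive men; the two passages must be reconciled, though the present point does not depend on it.

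**The concern.** HIV status is fixed before randomisation, has to be recorded to apply the entry rule, and is the one baseline factor for which the article itself reports an STI difference. Neither the allocation as described nor the univariable comparison uses it. The multivariable Poisson model could use it, but nothing commits the trial to that.

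Two things follow. First, if chance puts more HIV-positive men in one arm, the unadjusted STI comparison moves even when the intervention does nothing. Second, STI is to be compared between arms in two ways, one univariable and one multivariable with unnamed covariates, and no order of precedence is given. The covariates and the headline STI result could then be settled after the baseline tests, or the results, have been seen. The article does not say that this will happen; it leaves the route open.

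STI deserves this care because the trial is open label. The Strengths section presents laboratory-confirmed STI as an advantage over other studies, and the Limitations section accepts that information bias is possible.

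**Working it through.** **The plan's own figure.** The Sample size calculation gives 64 per group for 7% against 25% at 80% power. Alpha and sidedness are not stated; 0.05 two-sided is assumed. With pooled variance and no continuity correction:

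n = [1.96 × √(2 × 0.16 × 0.84) + 0.8416 × √(0.07 × 0.93 + 0.25 × 0.75)]² / 0.18² = (1.016 + 0.423)² / 0.0324 = 63.9, so 64.

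Then 128 × 1.10 = 140.8, so 141. Both stated figures are reproduced. Nothing below changes them.

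**Inputs for the STI check.**
- HIV-positive share q = 95 / (95 + 107) = 0.47, from the MS2 cohort (Background). Applying it to the trial is an assumption, because other men are recruited directly from the clinic.
- 150 men, 75 per arm. The 1:1 ratio is inferred from the equal group sizes.
- STI positivity of 18% and 30%, per visit. Applying these clinic-wide figures to trial entrants is an assumption.
- Four visits, from three-monthly screening over one year. The within-person correlation (ICC) is assumed to lie between 0 and 0.2.

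**Step 1: how often the arms differ.** SD of the difference in HIV-positive share ≈ √(2q(1 − q)/75) = √(2 × 0.47 × 0.53 / 75) = 0.082, or 8.2 points. 150 × 0.47 is about 70.5, so the count was taken as 70 or 71. Exact hypergeometric probabilities:

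| Difference in HIV-positive share | 71 HIV-positive | 70 HIV-positive |
|---|---|---|
| 10 points or more | 19% | 25% |
| 15 points or more | 5% | 7% |
| 20 points or more | 2% | 1% |

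The spread between columns arises only because the difference moves in steps of 2/75. The normal approximation gives 22%.

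**Step 2: what a difference does to STI.** Mean positivity = 0.18 + 0.12 × 0.47 = 0.236. A difference D in HIV-positive share produces a spurious STI difference of 0.12 × D.
- D = 10 points: 1.2 points per visit; ratio (0.236 + 0.006)/(0.236 − 0.006) = 1.05.
- D = 20 points: 2.4 points per visit; ratio 1.11.
- If the gap among entrants were 6 points rather than 12 (an illustrative assumption), D = 10 points gives 0.6 points and a ratio of about 1.03.

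**Step 3: set against sampling error.** SE = √{2 × 0.236 × 0.764 × (1 + 3 × ICC) / (75 × 4)}.
- ICC 0: 3.5 points. ICC 0.2: 4.4 points.
- The 1.2-point shift is therefore 0.27 to 0.35 SE.
- With no effect, the 95% range of the ratio from sampling alone is exp(±1.96 × SE/0.236): about 0.75 to 1.33 at ICC 0, and 0.70 to 1.44 at ICC 0.2.

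**Step 4: error rate and precision.** Given a 10-point difference, the two-sided type I error is 5.9% to 6.4%; given 20 points, 8.5% to 10.6%. Averaged over all randomisations it stays near 5%. HIV status explains about 2% of the variance of a single-visit result and 5% to 8% of a four-visit mean, so adjustment reduces the SE by 1 − √(1 − 0.05) to 1 − √(1 − 0.08), about 2.5% to 4%.

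**The case against.** The strongest case against has four parts.

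**A multivariable STI model is already planned.** This is correct. A reader might infer from the logistic sentence that every arm comparison is univariable and that the plan cannot correct for HIV imbalance. The documents do not support that: the Poisson analysis covers incident STIs and compares the arms. What stands is narrower. Its covariates are unnamed, and it sits beside a univariable analysis of the same outcome with no statement of which prevails.

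**Silence in an article is not an omission from the plan.** Stratification factors and covariate lists may be in the full protocol or analysis plan, which are not shown. So the article cannot be faulted for not mentioning stratification, and it cannot be read as saying that there is none. The univariable model, however, is a stated choice, and it can be improved on.

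**HIV status may not strongly predict STI in this trial.** A reader might take 18% against 30% as the gap among participants. Those figures describe all MSM attending the clinic. HIV-negative entrants need two STIs or a PEP treatment, which selects for higher risk and may narrow the gap. The 25% per visit reported for MS2 is not split by HIV status. This objection stands, and it makes the sizes above conditional.

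**The effect is small and already covered by the standard error.** This largely stands. Unstratified blocks are valid, and chance imbalance is not systematic bias. The counterpoint is that adjustment costs almost nothing and protects the particular allocation that the trial obtains.

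**Conclusion.** The point holds as a minor recommendation on the secondary STI comparison. The article specifies a univariable comparison, plans a multivariable one without naming covariates, and does not rank them, although a baseline factor related to STI in the clinic population has to be recorded for eligibility anyway.

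A difference of 10 points or more in the HIV-positive share has a probability of about 19% to 25%. At 10 points the STI ratio shifts by about 5%, or about 0.3 SE, and less if the gap among entrants is narrower than among clinic attendees. A 20-point difference would shift it by about 11% but has a probability of only 1% to 2%. These figures rest on the MS2 mix, 75 men per arm, the clinic-wide positivity figures, four visits and the assumed ICC range.

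It would go too far to conclude that the allocation is invalid, that the STI test has an inflated overall error rate, or that the primary result is at risk. Overall type I error stays near 5%, the primary sample size is unaffected, and the documents give no figure linking HIV status to help seeking.

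**What to change.** In the Statistical analysis section:

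1. Name the repeated-measures Poisson model, with arm and HIV status at entry as prespecified covariates, as the governing comparison for STI incidence.
2. Keep the univariable STI result as supportive.
3. State that these covariates are fixed in advance and do not depend on the baseline tests.

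If recruitment has not begun, the computer-generated blocks may also be stratified by HIV status. Two strata of roughly 70 to 80 men are workable with blocks of 8 or fewer. This is optional and means maintaining two lists. If recruitment has begun, leave the list alone and rely on the covariate. Adding HIV status to the primary logistic model is likewise optional.

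The cost is one covariate that is already collected. The return is modest: removal of the distortion from chance imbalance on HIV status, about 2.5% to 4% off the standard error under the assumptions above, and one clearly designated STI result.

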**Fig. 1 Fig1:**
[figure not shown]
Study design of the syn.bas.in open-label randomized controlled trial with a behavioural intervention to stimulate help seeking behaviour for mental health and addiction problems among MSM at the STI clinic of Amsterdam

### Assessments

Previous research has shown associations with HIV positivity and/or risk behavior and several syndemic domains like sexual compulsivity, drug or alcohol use, depression, stress, partner violence, childhood sexual abuse and discrimination [4, 12–14]. Questionnaires on these syndemic domains are added to this intervention. We hypothesized that people with ADHD may engage in risky sexual practices due to problems with impulsivity. Alexithymia might be an important factor associated with depression or anxiety. Therefor alexithymia and ADHD are added on to the list of syndemic domains and the following self-administered questionnaires are used (Table 1).

The Sexual Compulsivity Scale (SCS) is a 10-item self-administered questionnaire that assesses the impact of sexual thoughts on daily functioning and the inability to control sexual thoughts or behaviours [15]. As a cut-off to designate sexual compulsivity (SC), we took a value equal to or above 24 [15].

For alcohol related problems the Alcohol Use Disorders Identification Test (AUDIT) is used. This is a 10–item questionnaire developed for identifying risky or harmful alcohol consumption as well as alcohol-dependence [16, 17].

For drug related problems the Drug Use Disorders Identification Test (DUDIT) is used. This is a 11-item screening instrument developed to identify non-alcohol drug use patterns and various drug-related problems [18].

For ADHD the Adult ADHD self-report scale(ASRS) is used. This is a 6-item screening instrument developed by the World Health Organization to identify adults with ADHD [19].

For anxiety and depression the Hospital Anxiety and Depression Scale (HADS) is used. This is a 14-item screening instrument, 7 items measuring anxiety and 7 items measuring depression [20]. The HADS was found to perform well in assessing anxiety disorders and depression in both somatic, psychiatric, primary care and the general population [21].

For alexithymia the Toronto Alexithymia Scale (TAS) is used. This is a 20-item screening instrument developed to identify persons with alexithymia [22, 23].

Furthermore, we asked for partner violence [13], childhood sexual abuse [13] and discrimination [24] as these variables have been associated with psychosocial health outcomes. (i.e. Did you experience any form of violence (symbolic (e.g., verbally, someone threatened you, stalked you) physical (e.g., someone hit you, kicked you) or sexual(e.g., someone forced you to have sex)) in the past 5 years with a primary partner?; Did you ever experience being ‘forced or frightened’ by someone into doing something sexual with a partner who was more then 10 years older at the moment when you were 16 years or younger?)

Tests used for STI screening in routine practise at the STI outpatient clinic of Amsterdam will be used in the study. The APTIMA ® Combo 2 assay is a Nucleid acid amplification test (NAAT) used to detect RNA of both *Chlamydia trachomatis* and *Neisseria gonorrhoeae* in the urethra, rectum and pharynx. The INNO-LIA Syphilis Score, Fujirebio/Innogentetics is used for syphilis serology. The Liaison® XL murex is used to detect antibodies for hepatitis B and hepatitis C. Both an Alere Determine HIV 1/2 rapid test and a 4th generation combo test (INNO-LIA™ HIV I/II Score, Fujirebio) are used for HIV screening.

Clinical data and biological materials will be stored according to the STI clinic procedures. Electronic patient files are accessible to all medical personnel of the STI clinic with access and codes to this system. All data gained from questionnaires will be kept under a unique project ID, which will be given at each participant at the beginning of the study based on the number of previous participants. A master list linking study ID’s to electronic patient file identifiers will be controlled by the study coordinator. The list will be kept in a locked filing cabinet with access restricted to the study coordinator.

### Sample size calculation

In the Amsterdam health monitor, 7% of the MSM respondents reported to have serious psychosocial problems [25]. Because of the lack of data, we hypothesize that 7% of the participants will already be in care for psychosocial problems. With our intervention we intend to increase help seeking behaviour from 7% to at least 25%. As 89% of the MS2 cohort used at least two different drugs [2], we assume that at least 40% will score above the DUDIT or AUDIT cut-off. Combined with the other questionnaires, including the ADHD, sexual compulsivity, alexithymia, anxiety and depression questionnaires, we expect that about 50% of the study population will score above the cut off of at least one syndemic domain questionnaires. Previous studies have shown that MSM at the STI clinic are willing to participate in STI clinic initiatives. Using the opting-out strategy for HIV-testing, refusals to test for HIV dropped from 38% to 2% within one year [26]. In the syn.bas.in study we will actively stimulate help seeking behaviour. Therefore we believe that an improvement in help seeking behaviour from 7% to at least 25% is a realistic estimate. To detect an increase of help seeking behaviour from 7% to 25% and a statistical power of at least 80%, at least 64 participants per group are needed. Taking into account 10% loss to follow up, at least 141 participants are needed. Our aim is therefore to recruit 150 participants.

### Statistical analysis

Descriptive statistics will be used to describe baseline characteristics, questionnaire scores, condom use, number of partners, number of unprotected anal sex partners, recreational drug use (during and outside sexual activities) and lost to follow up rate. The distribution of the characteristics of the two intervention groups will be compared using Chi-squared tests for categorical data and student t-test or rank sum tests for continuous data depending on the distribution of the characteristics. To assess to effect of the intervention (control group vs. experimental group) on the primary outcome variable (help seeking behaviour), a univariable logistic regression analysis will be performed. Similar analyses will be performed with the secondary outcome variables. Changes over time will be described for the following parameters: drug use, risk behaviour and incident STIs. We will use appropriate univariable and multivariable statistical methods (poisson regression), corrected for repeated measurements within individuals to investigate changes over time and associated determinants. These analyses will be conducted comparing the two intervention groups.

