### Study intervention

All participants will receive standard care, including STI screenings every three months and offered a motivational interviewing based counseling session. STI screenings include tests for syphilis, hepatitis B - if not documented vaccinated - hepatitis C, HIV, and anal, urethral and pharyngeal chlamydia and gonorrhea. Asymptomatic men will be screened using a fast track procedure - i.e. no physical examination and self-sampling. Symptomatic men - with suspected STI related signs and/or complaints - will get a full physical examination, including anoscopy. Treatment and contact tracing will be offered to those with a newly diagnosed infection. At the initiative of the participant (e.g. in case of STI related complaints) additional screening will be available.

After explanation of the study by a study healthcare provider and informed consent is obtained, participants will be randomized either to the intervention or the control group. After intake, and at the final visit of the study, all participants fill out a set of questionnaires. Questionnaires will be sent via email and represent various syndemic domains (Table 1).

**Table 1 Tab1:** Questionnaires on syndemic domains that will be used in the syn.bas.in study for referral of MSM showing high risk behaviour at the STI clinic of Amsterdam

Syndemic domain	Questionnaire	Cut off (range)
Sex addiction	Sexual Compulsivity Scale [15]	≥ 24 (10–40)
Alcohol/drug addiction	AUDIT[17] DUDIT [18]	AUDIT ≥8 (0–12) DUDIT ≥8 (0–40)
Anxiety	Hospital Anxiety Depression Scale [20]	≥8 (0–21)
Depression	Hospital Anxiety Depression Scale [20]	≥8 (0–21)
ADHD	Adult ADHD Self Report Scale [19]	≥4 (0–6)
Alexithymia	TAS-20 [22, 23]	≥52 (20–100)
Partner violence	Stall [13, 24]	/
Childhood sexual abuse	Stall [13, 24]	/
Discrimination	Stall [13, 24]	/

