Participants in the intervention arm will be offered the questionnaires a second time before their subsequent three-monthly follow-up visit. During these subsequent visit the outcome of all questionnaires will be discussed to provide the participant in the intervention group a better insight in potential mental and/or addiction problem(s) that possibly contribute to risk behaviour. Via feedback and motivational interviewing the willingness to seek help will be evoked and monitored. All study healthcare providers receive training by mental health care providers to address these issues and are available for consultation in between visits, if necessary. If help is accepted, participants will be referred to a relevant mental health or addiction treatment service. Since co-located care may help to reduce barriers and improve health seeking behavior, intake consultations are available at the STI outpatient clinic of Amsterdam.

Participants in the control group receive standard STI screening and motivational interviewing based counseling session, yet controls are offered the questionnaires only during initial and end visit and do not receive feedback on the results of the questionnaires. Controls are allowed to visit the co-located care. After one year, participants in both groups will be asked to fill out the initial questionnaires again.

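### The primary outcome's univariable logistic regression is extended to secondary outcomes that are counts or rates, and the form of the Poisson correction, which decides whether intervals for partner counts are sound, is left open

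*Protocol article*

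**What the plan says.** The Statistical analysis section of the protocol article states that, for help seeking, "a univariable logistic regression analysis will be performed". It continues: "Similar analyses will be performed with the secondary outcome variables".

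The Secondary outcomes section lists STI incidence and changes in sexual risk behaviour, namely "condom use/number of partners/ number of unsafe partners/amount anal sex/recreational drug use/renounce to visit the STI clinic". The list is mixed. Numbers of partners and of unsafe partners are counts, STI incidence is a rate, and others are or can easily be yes/no.

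A second layer of analysis follows: "Changes over time will be described for the following parameters: drug use, risk behaviour and incident STIs". For this layer: "We will use appropriate univariable and multivariable statistical methods (poisson regression), corrected for repeated measurements within individuals". The arms are compared here too: "These analyses will be conducted comparing the two intervention groups".

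The text does not pair outcomes with models, and it does not say what form the correction for repetition takes.

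On data collection, the Study intervention section gives both arms three-monthly STI screening and adds: "At the initiative of the participant (e.g. in case of STI related complaints) additional screening will be available". On the syndemic questionnaires it says: "Participants in the intervention arm will be offered the questionnaires a second time before their subsequent three-monthly follow-up visit". Controls receive those questionnaires only at the start and the end.

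**The concern.** Logistic regression needs a yes/no response. Applied to a partner count or an STI count, it forces a cut-point. None is given, the distances between men on the same side of it are lost, and a univariable model takes no account of where each man started. The stated outcomes are changes in behaviour, so baseline is the covariate most likely to sharpen the comparison.

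The Poisson layer raises a separate question. Poisson regression takes the variance to equal the mean, and partner counts in a group selected for high risk are likely to be far more spread out than that. Correcting for repetition is not the same as correcting for overdispersion. Some corrections deal with both, others only with the first.

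At stake are the secondary comparisons. The research question in the Background asks about risk behaviour as well as help seeking, and the Strengths section puts weight on laboratory-confirmed STI results.

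**Working it through.** **The plan's own figure.** The only sample-size figure concerns the primary outcome. With 7% against 25%, 80% power and two-sided 5% (assumed, since alpha is not stated), the pooled-variance formula gives n = [1.960·√(2·0.16·0.84) + 0.842·√(0.07·0.93 + 0.25·0.75)]² / 0.18² = (1.016 + 0.423)² / 0.0324 = 63.9, so 64 per group, as stated. It does not bear on this point except to supply the group size used below. The article gives no distribution for any secondary count.

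**1. Cost of dichotomising a count.** The Background reports a new STI at 25% of visits with four screenings a year. Taking this as 0.25 STIs per visit, the yearly mean is μ = 4 × 0.25 = 1.0.

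- Poisson count: information on the log rate is μ = 1.0. The any-versus-none version carries μ²e^(−μ)/(1 − e^(−μ)) = 0.368/0.632 = 0.58, so 58% is kept.
- Rates that differ between men by a gamma with shape k (assumed 0.5 to 2): full information is μ/(1 + μ/k), P(none) is p₀ = (1 + μ/k)^(−k), and the dichotomised information is [μ(1 + μ/k)^(−k−1)]² / [p₀(1 − p₀)].

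| k | full | dichotomised | kept |
|---|---|---|---|
| 2 | 0.667 | 0.356 | 53% |
| 1 | 0.500 | 0.250 | 50% |
| 0.5 | 0.333 | 0.152 | 46% |

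The standard error therefore grows by a factor of 1/√0.58 = 1.31 to 1/√0.455 = 1.48. Another cut-point would give another figure, and the article names none.

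**2. What the Poisson correction does to the error rate.** These are null simulations with nominal 5%, 4,000 to 5,000 replicates, and all dispersion values assumed.

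Arm effect, four visits, 64 or 75 men per arm:

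| Outcome | plain Poisson SE | cluster-robust SE |
|---|---|---|
| Partners, mean 5 to 10 per visit, between-man gamma shape 0.5 to 1 | 69–84% | 5.6–6.9% |
| STIs, 0.25 per visit, gamma shape 0.5 to 2 | 11–26% | 5.6–6.4% |

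The plain Poisson column is not the planned analysis. It shows only what the correction has to repair.

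Arm-by-time effect, two time points, 64 per arm, between-man gamma shape 1:

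| Mean | extra visit-level gamma shape | per-man intercept, model SE | cluster-robust SE |
|---|---|---|---|
| 10 | none | 5.0% | 5.6% |
| 10 | 5 | 36.8% | 6.5% |
| 10 | 2 | 55.1% | 6.6% |
| 10 | 1 | 66.4% | 7.6% |
| 5 | 2 | 43.4% | 7.2% |
| 1 | none | 5.3% | 6.1% |

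A per-man intercept absorbs differences between men. It does not absorb extra variation from visit to visit within a man. A sandwich variance covers both, at a level slightly above 5% with this group size.

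**3. Testing and time points.** Scheduled screening is the same in both arms, and extra tests on request are open to both. If one arm alone had 0.1 to 1.0 extra tests a year at the same 25% yield, its detected STIs would be multiplied by (4 + 0.1)/4 = 1.025 to (4 + 1)/4 = 1.25. No passage supplies such a difference between arms. The additional questionnaires in the intervention arm are the Table 1 set. They do not measure condom use or partner numbers, and among the secondary outcomes at most the alcohol and drug scores are touched.

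**The case against.** The plan can be read generously. The similar analyses may only mean univariable comparisons between arms, several listed outcomes are naturally yes/no, and dichotomising a count is wasteful but not invalid. Poisson regression is a standard model for incidence, the text speaks of appropriate methods, and the type of correction and any offset are details that a condensed article may leave to a fuller plan. All of that stands, and it limits the weight of the point. It does not remove the literal instruction, which carries a logistic model over to outcomes that are counts and rates.

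A reader might go further and infer three stronger things, which the document does not support.

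- *That intervals for partner counts will be wrong.* The largest error rates belong to an uncorrected Poisson model. The article plans a corrected one, and if the correction is GEE or a sandwich variance the intervals are close to right.
- *That STI detection will be biased between arms.* Schedule and access to extra tests are the same in both. A difference in attendance is conceivable in an open-label trial, but its size and direction are unknown.
- *That behaviour will be compared at different times in the two arms.* The extra questionnaires are the syndemic set. The article does not say that partner or condom data are collected on a different schedule by arm.

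**Conclusion.** The concern holds in a limited form. As written, the plan applies univariable logistic regression to count and rate outcomes. This loses information (42% to 54% of it in the STI illustration, which assumes 0.25 STIs per visit, four visits, an any-versus-none cut and gamma shapes down to 0.5) and ignores baseline. The Poisson analysis is adequate under GEE or a sandwich variance. It may give intervals that are too narrow if the correction is a random intercept with model-based standard errors and counts vary extra from visit to visit. The article does not say which applies, so this second part is a condition to settle, not a demonstrated error. The dispersion values are assumptions throughout. The primary analysis and the sample size are not affected. The point is worth acting on because it bears on every count outcome among the secondary endpoints and is nearly free to correct.

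**What to change.** Replace the sentence on similar analyses with a short outcome-by-outcome statement:

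- **Partner and unsafe-partner counts:** negative binomial regression, or Poisson regression with a sandwich (GEE) variance, adjusted for the baseline count. Drop the univariable logistic analysis of these outcomes.
- **Yes/no outcomes (such as condom use and drug use recorded as yes/no):** keep logistic regression, with GEE where measurements repeat.
- **STI incidence:** a count model with a log offset for follow-up or tested person-time. Add a sensitivity analysis restricted to the scheduled quarterly tests. This should not be the main analysis, because it leaves out infections found and treated between visits.
- **Questionnaire scores, where used as outcomes:** compare arms only at baseline and the one-year visit, which both arms share.
- **Repeated measurements:** name the correction and state that it allows for overdispersion.

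The cost is a revised paragraph, a little programming and possibly wider intervals. Sample size and data collection stay as they are.
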